## Abstract

**Background:**

Borderline intellectual functioning (BIF) is defined as a “health meta-condition… characterized by various cognitive dysfunctions associated with an intellectual quotient (IQ) between 71 and 85 which determines a deficit in the individual’s functioning both in the restriction of activities and in the limitation of social participation”. It can be caused by many factors, including a disadvantaged background and prematurity. BIF affects 7–12% of primary school children that show academic difficulties due to poor executive functioning. In many children with BIF, language, movement and social abilities are also affected, making it difficult to take part in daily activities. Dropping out of school and psychological afflictions such as anxiety and depression are common in children with BIF.

This study investigates whether an intensive rehabilitation program that involves all of the areas affected in children with BIF (Movement, Cognition and Narration of emotions, MCNT) is more effective than Standard Speech Therapy (SST).

**Methods:**

This is a multicenter interventional single blind randomized controlled study. Children aged between 6 to 11 years who attend a mainstream primary school and have multiple learning difficulties, behavioral problems and an IQ ranging between 85 to 70 have been enrolled. Participants are randomly allocated to one of three groups. The first group receives individual treatment with SST for 45 min, twice a week for 9 months. The second group receives the experimental treatment MCNT for 3 h per day, 5 days/ week for 9 months and children work in small groups. The third group consists of children on a waiting list for the SST for nine months.

**Discussion:**

BIF is a very frequent condition with no ad hoc treatment. Over the long term, there is a high risk to develop psychiatric disorders in adulthood. Due to its high social impact, we consider it very important to intervene during childhood so as to intercept the remarkable plasticity of the developing brain.

**Trial registration:**

“Study Let them grow: A new intensive and multimodal Treatment for children with borderline intellectual functioning based on Movement, Cognition and Narration of emotions”, retrospectively registered in ISRCTN Register with ISRCTN81710297 at 2017–01-09.

## Background

Borderline Intellectual Functioning (BIF) is a complex clinical entity that has received poor scientific investigation [1, 2]. According to the CONFIL consensus group [3], BIF can be defined as a “*health meta-condition … characterized by various cognitive dysfunctions associated with an intellectual quotient (IQ) between 71 and 85 which determines a deficit in the individual’s functioning both in the restriction of activities and in the limitation of social participation*”. Excluding BIF due to genetic and chromosomal abnormalities syndromes, the mostly frequent causes related to this condition are biological factors, like perinatal complications, and epigenetic factors related to the social environment such as maltreatment, abuse, neglect and high level of maternal stress [1, 4–7]. It is estimated that the prevalence of “non genetic” BIF ranges between 7 to 12% [2, 3] but the lack of terminological consensus and specific diagnostic code in the DSM-V [8] and ICD10 [9] makes it difficult to have a precise estimate. In DSM-V IQ test scores are removed from the diagnostic description and BIF is mentioned only within V-codes; this makes the BIF condition more difficult to be defined and acknowledged [2, 10].

BIF is associated with several neurodevelopmental disorders, with a high frequency for anxiety and behavioral disorders [1, 2, 11–14]. A strong association between BIF and mental disorders is observed in adolescence and in adulthood (e.g. antisocial personality disorder, depression, psychosis, suicide and substance abuse) [12, 15, 16]. The comorbidity with mental disorders is of great relevance in the prognosis: presence of BIF adds further severity to the evolution of psychiatric diseases [17]. Moreover, BIF is a lifelong condition with obvious drawbacks in terms of social and vocational opportunities and health outcomes [1, 13, 15, 18]. A longitudinal study of the impact that mild intellectual deficits, including BIF, have on the life course demonstrated that low-IQ individuals, compared to their higher IQ siblings, completed less schooling, had less prestigious occupations, rated themselves less physically healthy, and reported lower levels of psychological well-being [19].

Furthermore, in childhood, BIF is associated with some degree of motor skills limitation and cognitive difficulties in gaining and generalizing knowledge, in executive functions (i.e. working memory, problem solving, attention and concentration, planning, and inhibition of impulsive responses) and text comprehension [3, 20, 21]. Indeed, children with BIF have a high rate of school failures [18, 22, 23].

Finally, in a recent study [24], we found that children of 7 to 10 years of age with BIF show a delay in the development of social competences. Specifically, they perform poorly on all types of false belief tasks that test the Theory of Mind. Their performance was comparable to children of a younger age (3 to 4 years) who understand that actions are driven by desires, thought, intention and true belief but do not comprehend that behavior can also be justified by misinterpretation, i.e., false belief. These difficulties can result in poor social relations and social disadvantage in adulthood.

Moreover, in a recent study [25] concerning brain morphometry in children with BIF, we detected a delayed development of the parahippocampal, temporal and sensory-motor cortices, important for behavioral, learning and motor abilities. Such delay was highly correlated with IQ indices. Considering the great amount of cerebral modifications that occur in the typical developing brain between 6 to 12 years of age [26–29], we believe that an early and effective intervention is essential to improve the clinical course and the brain development trajectory of children with BIF.

For this reason, we developed an innovative treatment for BIF that stems from three main theoretical considerations: 1- Intelligence is not a fixed entity but a multidimensional and dynamic process; 2- the development of emotional, cognitive and motor skills is interrelated; 3-. environmental enrichment (EE) has a high impact on the neurodevelopment.

In relation to the first point, we considered the definition of intelligence of the Mainstream Science on Intelligence [30], “*It is a very general mental capability that, among other things, involves the ability to reason, plan, solve problems, think abstractly, comprehend complex ideas, learn quickly and learn from experience*”. According to this definition, intelligence can be considered a modifiable entity that is largely dependent on educational, cultural, socioeconomic, emotional and motivational factors. This notion is supported by both behavioral and neuroimaging data [31] showing that individual’s intellectual capacity can decrease or increase in the teenage years and also correlate with independently measured changes in brain structure of specific regions. We consider intelligence important for the development of truly adaptive abilities that ultimately represents a protective factor from social disadvantage in adulthood.

Point 2 refers to recent findings demonstrating that the level of performance in motor, executive functioning and language skills is highly correlated in both typical development [32–37] and in children with BIF [38, 39]. Moreover, the development of the brain areas involved in these functions is closely interrelated [40].

Finally, the third point is related to the well known effect of EE on neurodevelopment: richer and more stimulating environments determine higher rates of synaptogenesis and more complex dendritic arbors, leading to increased brain activity. EE was originally demonstrated in mouse brain [41–43] and successively confirmed on humans [44–47]. Research in humans has shown that attaining and engaging in higher levels of education and living in cognitively stimulating environments results in greater cognitive reserve [48]. The effects of EE take place primarily during neurodevelopment, but also throughout adulthood to a lesser degree [49, 50]. In humans, the opposite phenomenon has also been demonstrated: lack of stimulation in childhood, a critical period for the neurodevelopment, causes delay and impairment in the cognitive development, as in the case of children growing in Institutions that offer impoverished stimulation [51]. Similarly, we consider important, for the rehabilitation of children with BIF, to include different and multiple levels of stimulation as specified in the Methods section. Moreover, we consider part of the EE the capacity to listen and understand in an empathic way the children, focusing not only on their performances but also on their needs and emotions promoting the use of creative strategies to learn instead of fixed predetermined instructions.

All the above-mentioned considerations have been crucial for our choice of a treatment for the BIF. We introduce an innovative, multimodal and intensive training called the Movement Cognition and Narration of emotions Treatment (MCNT). No specific rehabilitation approach is available at the moment for children with BIF, but due to their poor academic performances they are typically treated with Standard Speech Therapy (SST). The latter is aimed at training specific functions such as writing or reading, and/or with the prescription to use facilitation devices such as the calculator and/or the computer.

The aim of our trial was to determine if the MCNT is more effective than SST in improving global intelligence in children with BIF. Our prediction is that MCNT will prove to be more effective than SST due to its use of a multimodal, empathic and game oriented approach, with the use of interactive technology devices, and a great variety of activities related to cognition, psychomotricity and emotions. The difficulties encountered by BIF children, indeed, cannot be delimited to a single specific domain. Consequently, we consider the SST approach as insufficient in treating a complex condition such as BIF. Furthermore, we predict that children with BIF attending the MCNT treatment will show a greater improvement also in the cognitive abilities and in particular, executive functioning. Finally, we will investigate if the MCNT improves the developmental trajectories of brain regions that we previously identified as having delayed maturation in children with BIF: the parahippocampal, temporal and sensory-motor cortices.

## Methods

### Study design

This is a multicentre interventional single blind randomized controlled study with three groups of children with BIF: group 1- children treated with SST (conventional treatment; *N* = 20); group 2-children treated with the MCNT (experimental treatment, *N* = 20); group 3-children not treated -on the waiting list for SST (no treatment *N* = 20).

The Study was approved by the Ethics Committee of the Don Gnocchi Foundation and of the ASST S. Paolo and S. Carlo Hospital.

All parents signed a written informed consent at the first meeting.

The primary and secondary outcome measures are determined at two time points, within two months prior to the beginning of the treatment (T0) and within two months after the end of the treatment (T1). Evaluations of all children made before and after treatment are performed by two psychologists blind to the type of intervention that the child receives. The flow diagram for study enrollment and randomization, as per Consolidated Standards Of Reporting Trial (CONSORT) guidelines, is shown in Fig. 1.

**Fig. 1 Fig1:**
[figure not shown]
Consolidated Standards Of Reporting Trial (CONSORT) guidelines flow diagram for enrollment and randomization

**Fig. 2 Fig2:**
[figure not shown]
Timeline of the trial. Timing and duration of the various procedures used in the trial

### Sample size

For the power calculation, considering preliminary data from our group, we expect a delta of 8 points (T1 –T0) in the primary outcome measure (WISC III FSIQ) between SST and MCNT groups, and 10 points between MCNT and no treatment group with a standard deviation of 10. With a sample size of 60, the calculation of the effect size is 0.43 and the probability is 0.83.

Standard procedures to maintain participants’ interest in the study and to avoid drop outs will be applied (regular meetings with teachers and parents of the children). Moreover, since the MCNT requires children to attend the treatment four day/week, we organized a shuttle that brings them from their school to our Centre brings, to avoid drop-outs.

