### Analysis

Statistical analyses on outcome measures will be conducted using R and SPSS. The General Linear Model (GLM) will be used to test the interaction effects between treatment (MCNT vs no treatment, MCNT vs TAU, TAU vs no treatment) and time (2 repeated measures, T0 and T1). Violations of the parametric model assumptions will be tested and explored with ad-hoc techniques. If violations will be detected, robust methods, data manipulation or statistical corrections will be applied accordingly. An intention-to-treat analysis approach will be used. The missing data process will be examined and the proper imputation method will be selected thereafter.

MRI data will be analyzed with specific statistical software: SPM12, (http://www.fil.ion.ucl.ac.uk/spm/); and FreeSurfer (https://surfer.nmr.mgh.harvard.edu/) and FSL (https://fsl.fmrib.ox.ac.uk/fsl/fslwiki/). Random effect analyses will be done to detect if there is an effect of treatment on the variables measured. The model will comprise a between factor level (group) and a within factor level (time). Demographic characteristics will be used as covariates if associated with the outcome measure.

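### The stated power of 0.83 fits the three-group omnibus test; the contrast named in the aim, MCNT vs SST, has about 0.69–0.70 (two-sided 5%) or 0.80 (one-sided 5%)

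*Protocol article*

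**What the plan says.** The Background of the protocol article states the main question as a two-arm comparison: "The aim of our trial was to determine if the MCNT is more effective than SST in improving global intelligence in children with BIF".

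The Sample size section gives the expected differences in FSIQ change. For SST against MCNT it says "we expect a delta of 8 points", and it then adds "10 points between MCNT and no treatment group with a standard deviation of 10". It concludes: "With a sample size of 60, the calculation of the effect size is 0.43 and the probability is 0.83". It does not name the test behind these figures, the significance level or whether the test is one- or two-sided. On attrition it describes retention measures only ("to avoid drop outs will be applied") and gives no expected loss.

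The Study design section allocates 20 children to each arm ("experimental treatment, *N* = 20"; "conventional treatment; *N* = 20"), with a third arm of 20 on the waiting list. The Analysis section tests treatment-by-time interactions and lists the treatment comparisons as "MCNT vs no treatment, MCNT vs TAU, TAU vs no treatment".

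**The concern.** The section gives one power figure and does not say which hypothesis it belongs to. The paragraph opens with the SST–MCNT difference, and the aim is MCNT against SST, so a reader will naturally take 0.83 as the chance of detecting the expected 8-point advantage over standard care. If 0.83 instead belongs to the statement that the three arms are not all equal, it answers another question. That statement can be established mainly by the larger gap between MCNT and no treatment.

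The stake is interpretation. A non-significant MCNT–SST result will look more informative than it is if readers believe that the comparison had 83% power. The same applies, more sharply, to SST vs no treatment, where the inputs imply a difference of only 2 points.

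**Working it through.** **Inputs**
- MCNT minus SST, difference in T1–T0 change: 8 points (Sample size).
- MCNT minus no treatment: 10 points (Sample size). Hence SST minus no treatment = 10 − 8 = 2 points.
- SD 10 (Sample size), read as the SD of the change score, common to all arms.
- 20 per arm, N = 60 (Study design, Sample size).
- Alpha and sidedness: not stated. Assumed 5%, with two-sided and one-sided both shown.

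**Step 1. Reproduce the stated figures.** Up to a constant, the mean changes are 10 (MCNT), 2 (SST) and 0 (no treatment), with grand mean 4.
- SD of the means = √[(6² + (−2)² + (−4)²)/3] = √(56/3) = 4.32.
- Cohen's f = 4.32/10 = 0.432, which matches the stated 0.43.
- Omnibus F test on change scores (equivalent to the 3-group × 2-time interaction): df 2 and 57, noncentrality λ = f²N = 0.1867 × 60 = 11.2, alpha 0.05. Power = 0.839, or 0.836 with f rounded to 0.43. The stated value is 0.83.

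**Step 2. Could the figures belong to MCNT vs SST?** For that pair, d = 8/10 = 0.80, and the two-group f is 0.80/2 = 0.40, not 0.43. The nearest power under any variant tried is 0.812 (one-sided 5%, normal approximation), and that variant does not yield an effect size of 0.43. Only the three-group reading fits both printed figures.

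**Step 3. Power for the contrasts listed in the Analysis section.** With two time points, the pairwise treatment-by-time interaction is the comparison of mean changes. Noncentral t with 20 per arm: δ = d × √(20 × 20/40) = 3.162d.

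| Contrast | Difference | d | δ | Power, two-sided 5%, 38 df |
|---|---|---|---|---|
| MCNT vs SST | 8 | 0.80 | 2.53 | 0.693 |
| MCNT vs no treatment | 10 | 1.00 | 3.16 | 0.869 |
| SST vs no treatment | 2 | 0.20 | 0.63 | 0.095 (0.0946) |

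**Step 4. How far MCNT vs SST moves with the assumptions**
- Two-sided 5%, error pooled over three arms (57 df): 0.701.
- Two-sided 5%, normal approximation: 0.716.
- One-sided 5%: 0.799 (38 df), 0.804 (57 df), 0.812 (normal approximation).

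The chance of missing a true 8-point difference is therefore 1 − 0.693 = 31% two-sided, or 1 − 0.799 = 20% one-sided, against 1 − 0.83 = 17% if the printed figure is taken to apply.

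**Step 5. Illustrations only.** The document gives no drop-out rate and plans no multiplicity correction. If 18 per arm were analysed (10% loss), two-sided power for MCNT vs SST would be 0.645. With Bonferroni over three contrasts (alpha 0.0167) and 20 per arm, it would be 0.516.

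**The case against.** **No printed figure is wrong.** This stands. Both 0.43 and 0.83 follow from the stated inputs. The section gives both differences and the total of 60, and nowhere says in so many words that 0.83 is the power for MCNT vs SST. A reader might infer that the protocol made an arithmetic error, or that it expressly claims 83% power for its key comparison. The text supports neither reading. What it supports is narrower: the single power figure is unlabelled, and the stated aim does not have that power.

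**The aim is directional and alpha is not stated.** This also stands. At one-sided 5% the power is about 0.80, and the gap to 0.83 is small. A flat statement that the risk of a miss is 31% therefore goes too far; it holds for a two-sided 5% test, the usual convention but an assumption here.

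**The omnibus test may be part of the plan.** The Analysis section could be read as an overall group-by-time interaction followed by the listed contrasts, so the omnibus calculation is not shown to be foreign to it. That does not help the power for the aim: a significant MCNT–SST contrast would still be needed, and requiring a significant omnibus test first cannot raise the probability above 0.69–0.70.

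**SD 10 might be the SD of a single score.** Power for MCNT vs SST would then depend on an unstated T0–T1 correlation r: 0.41 at r = 0, 0.69 at r = 0.5, 0.89 at r = 0.7. But under that reading the omnibus figure would move too (0.53, 0.84 and 0.97), and 0.83 would reproduce only near r = 0.5, where the SD of change is again 10.

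**Drop-out and multiplicity.** A reader might infer from the shuttle and the family meetings that substantial loss is expected, or that a correction must cut power to about one half. The document gives no rate and plans no such correction, so those figures cannot carry the point.

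**Conclusion.** The point holds as a mismatch between the power figure and the stated aim. The pair 0.43 and 0.83 fits the three-group omnibus F test (means 10, 2, 0; SD of change 10; N = 60; alpha 0.05). This attribution is inferred, because no test is named.

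For the contrast in the aim, power is about 0.69–0.70 at two-sided 5% and about 0.80 at one-sided 5%. The shortfall against 0.83 is thus about 13–14 percentage points or about 3, depending on a choice that the document does not state. Both values assume that all 40 children in the two arms supply T1 data. MCNT vs no treatment is well powered at about 0.87. SST vs no treatment, at about 0.09, can barely detect the implied 2 points.

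The shortfall does not bias the estimates or affect type I error, and it does not show that the trial must enrol more children. It bears on how a non-significant MCNT–SST or SST–no treatment result may be read.

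**What to change.** Revise the Sample size section as follows:
- Label 0.43 as Cohen's f for three groups and 0.83 as the power of the omnibus test, once the sponsor has confirmed that this was the calculation.
- State alpha and sidedness, and say that the SD of 10 is that of the T1–T0 change.
- Add the pairwise powers at 20 per arm. At two-sided 5% these are MCNT vs SST about 0.69, MCNT vs no treatment about 0.87 and SST vs no treatment (implied 2 points) about 0.09. If a one-sided 5% test is intended, the figure for MCNT vs SST is about 0.80.
- Say that these figures assume complete T1 data, and that a non-significant MCNT–SST or SST–no treatment result is not evidence of no difference.

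Any figure under drop-out or a multiplicity correction should be marked as an illustration unless the sponsor adopts the underlying assumption. The cost is wording and a less favourable number for the main question. All three planned contrasts and the enrolment of 60 stay as they are.

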### Participants

Sixty participants will be consecutively recruited from the Child and Adolescent Neuropsychiatry Unit of IRCCS Don Carlo Gnocchi Foundation and of the ASST S. Paolo and S. Carlo Hospital.

Inclusion criteria are: age range between 6 to 11 years old and attending primary mainstream school; with a Full Scale Intelligence Quotient (FSIQ) score ranging from 70 to 85 determined with the Wechsler Intelligence Scale for Children-III (WISC-III) [52, 53]; presence of learning disabilities assessed with the standardized test battery for developmental dyslexia and dysorthographia (DDE-2) [54] and dyscalculia (AC-MT 6–11) [55]; difficulties in executive functions and or verbal comprehension assessed with Modified Barrage bell test (MBT) [56],Tower of London (TOL) [57, 58], and the Test of Reception of Grammar (TROG 2) [59, 60]; presence of an impact on daily life of the above mentioned difficulties as measured by the Child Behavioral Checklist (CBCL 6–18) [61, 62] and Vineland 2 [63].

The exclusion criteria are: presence of major neuropsychiatric disorders (such as ADHD and autism spectrum disorder); presence of neurological conditions such as epilepsy, traumatic brain injury, brain malformations and infectious disease involving the central nervous system. Moreover, the presence of systemic diseases such as diabetes or dysimmune disorders, genetic syndromes such as Down syndrome or Fragile X syndrome and a positive history for psychoactive drugs, particularly referring to current or past use of psychostimulants, neuroleptics, antidepressants, benzodiazepines and antiepileptic drugs are also considered exclusion criteria.

